# The Strengthening Exercises in Shoulder Impingement trial (The SExSI-trial) investigating the effectiveness of a simple add-on shoulder strengthening exercise programme in patients with long-lasting subacromial impingement syndrome: Study protocol for a pragmatic, assessor blinded, parallel-group, randomised, controlled trial

**DOI:** 10.1186/s13063-018-2509-7

**Published:** 2018-03-02

**Keywords:** Shoulder, Impingement, Pragmatic, Strength, Progressive, Exercise, RCT, Rotator cuff, Adherence, Sensitisation

## Abstract

**Background:**

Subacromial impingement syndrome (SIS) is a painful, and often long lasting, shoulder condition affecting patient function and quality of life. In a recent study, we observed major strength impairments in shoulder external rotation and abduction (~30%) in a population of patients with pronounced and long-lasting SIS. However, the current rehabilitation of such strength impairments may be inadequate, with novel rehabilitation programmes including exercise therapy only improving external rotation strength by 4–13%.

As these previous studies are the basis of current practice, this suggests that the strengthening component could be inadequate in the rehabilitation of these patients, and it seems likely that more emphasis should be placed on intensifying this part of the rehabilitation.

The purpose of this study is to investigate the effectiveness of a programme consisting of progressive home-based resistance training using an elastic band, aimed at improving shoulder external rotation and abduction strength, added to usual care and initiated shortly after diagnosis has been established.

**Methods:**

A pragmatic randomised controlled superiority trial will be conducted, including 200 patients with pronounced and long-lasting SIS, diagnosed using predefined criteria. Participants will be randomised to receive either an add-on intervention of progressive home-based resistance training using an elastic band in addition to usual care or usual care alone in a 1:1 allocation ratio. The randomisation sequence is computer generated, with permuted blocks of random sizes. The primary outcome will be change in Shoulder Pain And Disability Index (SPADI) score from baseline to 16 weeks follow-up. Outcome assessors are blinded to group allocation. Intervention receivers will be kept blind to treatment allocation through minimal information about the content of the add-on intervention and control condition until group allocation is final. Analyses are performed by blinded data analysts.

**Discussion:**

If effective, the simple shoulder strengthening exercise programme investigated in this trial could easily be added to usual care. The usefulness of the trial is further supported by the magnitude of the problem, the information gained from the study and the pragmatism, patient centeredness and transparency of the trial.

**Trial registration:**

The trial is pre-registered at ClinicalTrials.gov with the ID NCT02747251 on April 19, 2016.

**Electronic supplementary material:**

The online version of this article (10.1186/s13063-018-2509-7) contains supplementary material, which is available to authorized users.

## Background

Shoulder disorders are the second most frequent musculoskeletal reason for contacting a general practitioner [1]. Nearly half of these incidents are categorised as subacromial impingement syndrome (SIS) [2], a painful, and often long lasting [3], condition affecting patient function and quality of life [4]. In Denmark, the incidence of SIS reported in primary care is approximately 8 per 1000 inhabitants per year [5]. Further, with an average yearly cost per incident case of shoulder disorder of €4000 [6], as reported in Sweden, the societal costs related to SIS are noteworthy. However, most of the costs (74%) are related to a sub-group of patients (12%) with high pain intensity and more pronounced and long-lasting disability [7]. In this sub-group, sick leave from paid work accounts for more than half (61%) of the costs [7].

The latest systematic review on the efficacy of exercise therapy in the treatment of SIS suggests that an exercise intervention improves patient-reported function and pain in patients with long-lasting SIS (≥ 3 months), to a degree equivalent to surgery followed by post-operative rehabilitation [8]. In addition, an intervention including specific exercises significantly reduced the amount of operations in patients on the waiting list for surgery for SIS [9]. Consistent with these studies, the Danish national clinical guidelines for treatment of SIS recommends an exercise intervention lasting at least 3 months [10]. However, it is unknown which specific components of the heterogeneous exercise interventions are associated with a better outcome [11] and, though not demonstrated in patients with long-lasting SIS, patient adherence to the prescribed exercise interventions is also likely to moderate the effects of such interventions.

### Mechanisms

Resistance training, aimed at strengthening the rotator cuff muscles and scapula stabilising muscles, is an important component of most novel exercise interventions for long-lasting SIS [9, 12, 13]. This seems relevant as patients with SIS have significant force impairments in both the glenohumeral and the scapulothoracic joint [4, 14, 15]. However, these force impairments are most pronounced in the glenohumeral joint, with a 33% deficit in external rotation force and a 29% deficit in abduction force compared to only 8% and 18% force deficit in protraction and retraction of the scapula, respectively [15]. This suggests that specific training of the glenohumeral muscles is especially relevant. Such specific resistance training of the, often degenerated [16], rotator cuff muscles and tendons also seems relevant as this training modality is known to improve muscle and tendon health through various pathways [17].

### Need for a trial

It is uncertain if the novel exercise intervention programmes, aimed at patients with long-lasting SIS, are focusing sufficiently on strengthening exercises. Accordingly, changes in muscle force are only tested in a few randomised controlled trials (RCTs), including resistance training in the rehabilitation of patients with SIS [12, 13, 18, 19]. In these studies, maximum force in external rotation increased by only 4–15% in average from baseline to follow-up in patients doing strengthening exercises [12, 13, 18, 19], which is far from restoring the 33% impairment in external rotation force previously reported [15]. Though strength gain may not be the primary aim of the intervention, the sparse effect on this objective outcome points towards a possible gap in the rehabilitation of patients with long-lasting SIS. This suggests that the exercise dose received by patients might have been too small, either because the prescribed resistance training programmes were too mild, or simply due to lack of adherence to the prescribed programmes. The trial described in this protocol will aim to investigate the effectiveness of adding a simple shoulder strengthening exercise programme to usual care in patients with long-lasting SIS.

### Existing knowledge

To further ensure that we do not initiate a redundant trial, we have performed a systematic literature review. On January 26, 2016, we performed a systematic literature search on controlled trials investigating the effect of resistance training in patients with SIS. We searched Medline via PubMed (86 hits) and Embase via OVID (38 hits) using search strings for condition (shoulder impingement) and intervention (resistance training). We also searched www.clinicaltrials.gov for registered (finalised, ongoing or planned) trials. We only identified one trial [18] in which the effect of resistance training was isolated as the active part of the intervention. Additionally, in a recent systematic review, only one study [20] investigating the effect of an exercise intervention in patients with persistent SIS was identified, and in that study the exercise intervention was compared to surgery. In conclusion, the existing evidence regarding the effect of resistance training in patients with persistent SIS is very limited and we therefore consider this to provide a clear-cut ethical, scientific and economic justification for the trial described in this protocol.

### Dose selection

As previously stated, the exercise dose received by patients might have been too small in previous studies, either because the prescribed resistance training programmes were too mild or simply due to lack of adherence to the prescribed programmes. In the study by Lombardi et al. [18], patients allocated to an intervention consisting of supervised strengthening exercises only increased 9% in external rotation strength (derived from Lombardi et al. [18]), which was not significantly different from the waiting list control group. As exercise sessions were supervised, this absence of effect is likely a consequence of the prescribed dose being too small, with exercises for flexion, extension, internal and external rotation performed twice a week in 8 weeks with 2 × 8 repetitions at 50% and 70% of 6RM, respectively. One way to efficiently increase the exercise dose in rehabilitation is to include home-based exercises, as was done in a study by Bennell et al. [12]. In that study, an intervention consisting of manual therapy and home exercises was found superior to placebo in improving abduction strength (significant 15% increase), but not external rotation strength (non-significant 4% increase), pain scores or patient-reported function at the end of treatment. The limited gains in shoulder strength observed in the study by Bennell et al. [12] might also be a consequence of an insufficient exercise dose received by the patients. However, it is difficult to determine whether the sparse improvements in shoulder strength are due to the programme being too mild or because of low adherence, as the amount of external resistance applied to exercises is not described. Nevertheless, exclusion of non-adherent patients from the analyses did not alter the results, indicating that the sparse improvements in shoulder strength were not only due to low adherence.

In the current study, we aim to increase the received dose of strengthening exercises aimed at the rotator cuff muscles in patients with long-lasting SIS without aggravating their symptoms and with minimal risk of adverse events. To achieve this, the intervention will start with exercises using low relative resistance but high volume (number of sets per session and frequency of sessions). This approach is also relevant, as resistance training with low intensity/resistance, high frequency and approximately 3–4 sets per muscle group is associated with the highest gains in muscle strength in untrained individuals [21]. All sets are to be continued to failure, as this maximises the gain in local muscle endurance [22]. Furthermore, the low resistance will minimise pain during exercises and protect the muscle from overload injuries, ensuring that all patients are able to complete the programme.

The focus of exercises is on isometric holds and slow dynamic strengthening with a long time under tension (TUT). A high TUT is achieved through exercises with a low contraction velocity and the inclusion of an isometric component to increase the exercise stimulus without increasing external resistance; this in turn reduces the peak load on the involved, and possibly damaged [16], muscles and tendons. Thus, exercises become safer and less painful, which again will allow patients to actually adhere to the exercise intervention. Furthermore, the isometric part will be performed with the shoulder in approximately 30–45 degrees of scaption, the position in which the compression forces on the supraspinatus muscle and tendon are lowest [23, 24]. Exercises will mainly focus on external rotation and abduction, functions in which both supraspinatus and infraspinatus muscles are highly active [25].

### Possible effect modifiers

Patients with long-lasting SIS have lower mechanical pressure pain thresholds (PPT), both at the shoulder region and in other anatomical regions (such as the tibialis anterior), which may reflect an increased manifestation of peripheral and central pain sensitisation [26]. Pain sensitisation modulates the patients’ pain experience and, furthermore, the presence of hyperalgesia or referred pain before decompression surgery significantly worsens the outcome after 3 months [26], while more pain catastrophizing is related to persistence of symptoms in patients with long-lasting SIS [27]. It therefore seems likely that manifestations of peripheral and central pain sensitisation, and peripheral adaptations to long-lasting pain, could also affect the outcome of an exercise intervention. This could be either through an alteration in adherence to the intervention due to pain sensitisation, or through other mechanisms related to central pain sensitisation and peripheral adaptations.

The effect of scapula function on treatment outcome in patients with SIS is often debated, and one could argue that the increased emphasis on rotator cuff muscles, as is proposed in the current trial, would neglect an important aspect of the rehabilitation. Accordingly, it has been suggested that rotator cuff emphasis should only be after scapula control is achieved, as insufficient dynamic stability of the scapula could cause abnormal shoulder kinematics and impingement symptoms [28]. Assuming this, the effect of the add-on intervention in the current study, focusing mainly on strengthening exercises for the rotator cuff, could be modified be the presence of scapula dyskinesis. However, Mulligan et al. [29] recently found that treatment outcome was not significantly different between patients randomised to scapula stabilisation first, or rotator cuff strengthening first, questioning the importance of maintaining a scapula focus in the beginning of rehabilitation.

### Explanation for choice of comparators

This study aims to investigate the effectiveness of adding a simple shoulder strengthening exercise programme to usual care in patients with long-lasting SIS. Therefore, the relevant control condition is usual care, which is to be compared to the intervention condition involving an add-on exercise programme and usual care.

This is relevant because usual care for patients that are covered by the Danish National Guidelines for Treatment of SIS [10], and hence have a medically justified need for general rehabilitation, is referral to general rehabilitation under the Danish health act § 140. Such rehabilitation is likely based on the most novel evidence from previously mentioned RCTs [12, 13, 18], where only limited gains in muscle strength are found. It therefore seems unlikely that the current treatment addresses the issue of glenohumeral muscle strength to a sufficient degree.

Furthermore, direct monitoring of adherence to the add-on intervention makes it possible to conduct secondary analysis, investigating the relationship between exercise adherence and changes in both strength and patient-reported function.

## Methods

### Objectives

#### Primary research question

Based on the literature reviewed in the “Background” section, we asked the following research question:

Is a 16-week simple home-based shoulder strengthening exercise programme, in addition to usual care, superior to usual care alone for improving patient-reported shoulder function 16 weeks after baseline, measured using the Shoulder Pain And Disability Index (SPADI), in patients with persistent (> 3 months) subacromial impingement syndrome referred to further examination at a hospital?

The research question was framed using the PICOT model [30] with the following options for each element:**P**opulation: Patients with persistent SIS (> 3 months)**I**ntervention: 16-week simple home-based shoulder strengthening exercise programme added to usual care**C**ontrol: Usual care**O**utcome: Patient-reported shoulder function**T**ime frame: 16 weeks after baseline

#### Primary objective

The primary objective is therefore to investigate the effectiveness of adding a 16-week simple home-based shoulder strengthening exercise programme to usual care, compared to usual care alone, on changes in patient-reported shoulder function (SPADI score) from baseline to end of treatment (16 weeks) in patients with SIS.

#### Primary research hypothesis

Our hypothesis is that a 16-week simple home-based shoulder strengthening exercise programme, in addition to usual care, is superior to usual care alone for improving patient-reported shoulder function 16 weeks after baseline, measured using the SPADI, in patients with persistent (> 3 months) subacromial impingement syndrome referred to further examination at a hospital.

#### Secondary objectives

To investigate the effectiveness of adding a 16-week simple home-based shoulder strengthening exercise programme to usual care, compared to usual care alone, on changes in shoulder abduction and external rotation strength from baseline to end of treatment (16 weeks) in patients with SIS.To investigate the modifying effects of pain sensitisation, pain catastrophizing and scapula function on the effectiveness of adding a 16-week simple home-based shoulder strengthening exercise programme to usual care, compared to usual care alone, on changes in patient-reported shoulder function and shoulder abduction and external rotation strength from baseline to end of treatment (16 weeks) in patients with SIS.To investigate the dose-response relationship between objectively monitored adherence to the add-on intervention and change in patient-reported shoulder function, shoulder abduction strength and external rotation strength.To investigate the relationship between central and peripheral pain sensitisation and change in patient-reported shoulder function, shoulder abduction strength and external rotation strength, and to what degree this is mediated through adherence to the intervention.

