For the following secondary outcomes, the main analysis will be conducted for the outcome at 16 weeks follow-up, reported as the difference between groups at 16 weeks follow-up.Temporal Summation of Pain (TSP), a measure of central excitability (range 0 to 10 cm on electronic Visual analogue scale). A higher degree of TSP has previously been found in patients with unilateral SIS compared to healthy controls [54], and the decrease in TSP after surgical intervention is reported to be associated with the outcome of surgery [26].Conditioned Pain Modulation (CPM), a measure of the attenuated pain response (increase in tolerated pressure) to a painful pressure stimulus during application of another painful pressure stimulus [55]. CPM is a proxy measure of the function of the endogenous analgesia system, and patients with SIS have a lower CPM compared to healthy controls [54].Pressure Pain Threshold (PPT) is a measure of local mechanical hyperalgesia. It measures how much mechanical pressure is needed to elicit the first onset of pain. PPT is measured in kPa as the threshold for first detection of pain. Patients with SIS have lower PPTs in the shoulder region when compared to matched controls, possibly indicating peripheral sensitisation of the nervous system [26].Scapular Dysfunction (yes/no), measured using the modified Scapula Assistance Test, assessing if scapula muscle dysfunction influences the shoulder disorder. The result of the modified Scapula Assistance Test is a judgement of either positive or negative.Scapula Dyskinesia (yes/no), measured using the Scapula Dyskinesis Test, the result of which is a judgment of either positive or negative test.Global Impression of Change, measured on a 7-point Likert scale ranging from ‘Much better, a very important improvement’ to ‘Much worse, an important aggravation’.Patient Acceptable Symptom State, measured as the dichotomous answer (yes/no) to a standardised question regarding the acceptability of the current state of the shoulder symptoms.

Other outcomes of interest will be pain during testing of external rotation MVC, abduction MVC and active abduction ROM, as reported by the participant on a numeric pain rating scale (0 to 10, 0 = no pain), using standardised verbal anchors for the instruction [50].

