#### Statistical methods – additional analyses

##### Subgroup analyses

For the outcomes SPADI score, abduction MVC and external rotation MVC, subgroup analyses investigating the modifying effect of scapula dysfunction, scapula dyskinesia, temporal summation of pain, conditioned pain modulation, pain pressure threshold (site 1) and pain catastrophizing, respectively, will be conducted. These will be performed using a cLMM, similar to the corresponding main analyses, but including a dichotomised value for the first measurement of the relevant variable as the interaction term and reporting the effect estimates for each subgroup.

The following sensitivity analyses will be performed for the primary outcome and reported together with the primary analyses in the primary trial report:A per protocol analysis, similar to the primary analysis, will be performed. From the IG, only patients who attended intervention appointments on weeks 0, 5 and 10 will be included in this analysis, while all patients in the CG will be included.Adjusted cLMM to adjust the effect of treatment allocation on SPADI score for any baseline differences between groups. Baseline variables will be included as covariates if (1) the difference between groups is more than 0.3 of the common SD for continuous outcomes, or (2) proportions are significantly different (*P* < 0.05) between groups, for binary outcomes.Sensitivity analyses to investigate the importance of the clinometric properties of the SPADI score may be relevant. This is based on a very recent study [58], which evaluates the SPADI score using the Rasch model. The study was published after initiation of this trial.

Three exploratory dose-response analyses will be performed. Only participants in the IG will be included in these analyses. First, the interacting effect of adherence to the intervention, TSP and CPM, on change in external rotation MVC, abduction MVC and SPADI score (outcomes), will be investigated. Secondly, whether the effect of TSP and CPM is mediated by adherence to the intervention will also be assessed. These analyses will be conducted as available-case analyses.

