For all included variables, data from each time-period (t_0_-t_1_, t_1_-t_2_ and t_2_-t_3_) will be included as repeated measurements in these analyses. The outcome variable is the change between first and last measurement in a time-period. ‘Adherence’ to the intervention is the total TUT in a time-period. ‘Central Pain Sensitization’ score (TSP or CPM) is the score from the last time-point in each time-period.

Additionally, results will also be presented for similar analyses adjusted for Usual Care, calculated for each time-period as the average of time spent on usual care, as reported by text-message, in all weeks included in the relevant time-period.

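### Secondary objective 4 covers central and peripheral pain sensitisation, but the analyses that match it use only the central measures, so its peripheral part has no matching analysis

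*Protocol article*

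**What the plan says.** **The objective.** Under Secondary objectives, the fourth item is "To investigate the relationship between central and peripheral pain sensitisation and change in patient-reported shoulder function". It adds the two strength outcomes and then asks "and to what degree this is mediated through adherence to the intervention". The exposure is thus sensitisation of both kinds, and the mediator is adherence.

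**The analyses.** The additional-analyses part of the statistical methods says "Three exploratory dose-response analyses will be performed", restricted to the intervention group and to available cases. The first examines "the interacting effect of adherence to the intervention, TSP and CPM, on change in external rotation MVC, abduction MVC and SPADI score". The second is stated as "whether the effect of TSP and CPM is mediated by adherence to the intervention will also be assessed". The paragraphs that follow define the variables. Adherence is the total time under tension in a period, and the sensitisation "score (TSP or CPM) is the score from the last time-point in each time-period". The label given to that score describes it as central.

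**The measures.** Under Secondary outcomes, TSP is described as reflecting central excitability and CPM as a proxy for the endogenous analgesia system. By contrast, "Pressure Pain Threshold (PPT) is a measure of local mechanical hyperalgesia", and the article says that lowered values at the shoulder possibly point to peripheral sensitisation.

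**The concern.** An objective names two kinds of exposure, and the analysis section fixes the variables for only one of them. This is not a detail left open for a later plan. The article lists the exposures, defines how the score is taken and labels it as central. A statistical analysis plan that followed the text would leave half of the objective without an estimate. One that added PPT would depart from the published list.

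The peripheral half is not incidental. The section on possible effect modifiers opens with PPT findings. It then argues that both peripheral and central sensitisation could affect the outcome of exercise, possibly by altering adherence, and that is the pathway objective 4 is meant to examine. If PPT were added only after the data had been seen, the choice would be post hoc. If it were left out without comment, part of a stated objective would go unreported.

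**Working it through.** No figure in the plan bears on this point, so the check sets the objective beside each place where a sensitisation measure enters an analysis.

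| Place in the article | TSP | CPM | PPT | Question answered |
|---|---|---|---|---|
| Secondary outcomes; Table 2, sensitisation block | yes | yes | yes | Does the intervention change the measure? (between groups) |
| Subgroup analyses, text | yes | yes | yes (site 1) | Does the first measurement, dichotomised, modify the treatment effect on SPADI and the two strength outcomes? (objective 2) |
| Dose-response analysis, interaction | yes | yes | no | In the intervention group, do adherence and sensitisation interact in relation to change? |
| Dose-response analysis, mediation | yes | yes | no | Does adherence mediate the effect of sensitisation on change? (objective 4) |

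1. Objective 4 needs a sensitisation measure as exposure, change in SPADI or strength as outcome, and adherence as mediator. Only the last two rows have that form.
2. In both rows the exposures are TSP and CPM, which the article itself classes as central.
3. PPT appears only in the first two rows. In the first it is an outcome. In the second it splits patients into subgroups so that the randomised contrast can be compared between them. An interaction of PPT with treatment is not the association of PPT with change among those who exercise, and it contains no adherence term.
4. The text announces three dose-response analyses but spells out two. The third might be the adherence-only question of objective 3, or the count might refer to the three outcomes. Neither reading brings in PPT.

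The gap is therefore confined to the peripheral part of objective 4, for both the relationship and its mediation.

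**The case against.** **PPT is analysed elsewhere.** This stands, and it limits the point. A reader might infer that peripheral sensitisation is never analysed, or that the planned sensitisation paper could speak only about central sensitisation. The documents do not support either inference. PPT at site 1 is planned as an effect modifier for the same three outcomes and as a between-group outcome, and the Dissemination policy gives that paper both of those topics as well as mediation.

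**The size cannot be counted.** One could multiply three outcomes by two questions to get a number of missing estimates. The plan does not fix such a number: the first analysis is an interaction, and similar analyses adjusted for usual care are also to be presented.

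**PPT is not a clean peripheral measure.** This also stands. The outcome section hedges the link, and the effect-modifier section says that lowered thresholds at the shoulder and at remote sites may reflect both peripheral and central sensitisation. Site 1 is not defined in the article.

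**Adding PPT would inherit a timing problem.** The score comes from the end of each period, whereas adherence accumulates during it, so the exposure is measured after its supposed mediator. This is a fair criticism of the mediation model for TSP and CPM too. It does not remove the mismatch.

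**The full protocol or analysis plan may cover it.** This cannot be excluded, since neither is shown. The published exposure list is nevertheless explicit, and it conflicts with the published objective.

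**The work is only exploratory.** This is true, and it is why the severity is low.

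**Conclusion.** The point holds in a narrow form: objective 4 and the analyses that match it do not agree, and the peripheral part of that objective has no planned estimate of its relationship with change or of mediation by adherence. The severity is minor. The affected analyses are exploratory, available-case and confined to the intervention group. The primary outcome, the randomised comparison and the sample size are unaffected.

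The conclusion rests on PPT being the intended peripheral measure, which the outcome section suggests but hedges, and on the unnamed third dose-response analysis not being about PPT, for which the text gives no hint. It does not support a claim that peripheral sensitisation goes unstudied in the trial.

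**What to change.** Before the analysis, do one of the following.

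- **Add PPT** beside TSP and CPM as a further exposure in the interaction and mediation analyses, and drop the purely central label from the score. First confirm that site 1 is the local shoulder site and that PPT is measured at the same visits as TSP and CPM. Table 2 lists all three in one block over the same interval, which suggests so, but the schedule figure and the additional file on instruments are not shown. Report the results as exploratory, and PPT as a possible rather than definite marker of peripheral sensitisation.
- **Or restrict objective 4** to central sensitisation, so that objective and analysis agree.

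With either choice, name the third dose-response analysis or correct the count. If PPT is added to the mediation model, the time order of score and adherence should be considered in the same revision.

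The first option costs a few lines of text, some further model runs and a few more exploratory tests. If the schedule is as Table 2 suggests, it needs no new data. The second is a wording change only, but it gives up a question that the background section motivates.
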